### Planned sample size

To calculate the sample size, we created an R [34] script (https://osf.io/va5db/) that uses the packages pwr (version 1.3–0) [35] and MBESS (version 4.6.0) [36,37]. Following the small-telescopes approach proposed by Simonsohn [38], we estimated a target effect size based on the original experiment. According to Simonsohn’s proposal, the target effect size would be the effect size that can be detected with a power of 33% in the original study. In Luhmann et al.’s study, the main results were obtained from a multiple regression analysis where IU and TA scores, and delay discount factor were included as predictors, and the percentage of trials in which a delayed choice was made, p(Wait), was included as the dependent variable. This analysis yielded significant regression coefficients for IU and delay discount, but not for TA. Based on this result, we considered two possible sample sizes to choose the most conservative one. In the original study, that multiple regression model had 3 degrees of freedom in the numerator and 45 in the denominator. For the omnibus regression, the effect size that could be detected with a 33% power in the original study is f^2^ = 0.081. The sample size required to detect that effect size in a multiple regression with a power of 95%, using an α = .05, would be of 215 participants. However, the main theoretical point is the relation between IU and the behavioural task, as measured by p(Wait). Focusing on the targeted correlation coefficient between IU and p(Wait), the effect size that can be detected with a 33% power in the original study is f^2^ = 0.049, and the sample size required to detect this effect with a power of 95% would be n = 266.

As mentioned before, we chose the most conservative sample size, n = 266. This sample would be 5.4 times the original sample, and lead to a highly powered experiment. Given that the recruitment will be carried out in batches, recruitment will stop as soon as at least 266 participants complete the task and match the data selection criteria described in the methods section.

### Statistical analysis

The analyses that will be carried out are derived directly from Luhmann et al. The R script with all of the analyses described are already available at https://osf.io/b8hfc/. The packages lm.beta (version 1.5–1) [39], papaja (version 0.1.0.9942) [40], patchwork (version 1.0.0) [41] and tidyverse (version 1.3.0) [42] are used in this script.

We will report the descriptives and zero-order correlations of the variables probability of waiting in the behavioural task [p(Wait)], IUS score, TA score, and discount factor [(1/1+k), DELAY-DISCOUNT]. We will add the descriptives and correlations also of the SUPPS-P Impulsive Behavior Scale. As in the case of Luhmann et al., the main analysis will be a hierarchical linear regression (see Table 1). Using p(Wait) as the dependent variable, two models will be considered: The first one will include TA and DELAY-DISCOUNT as predictors (Model 1), and the second model will include IU as an additional predictor (Model 2). Extending Luhmann et al.’s study, an additional hierarchical linear regression analysis will be conducted. The Model 1, that has TA and DELAY-DISCOUNT as predictors will be compared with a model that also includes SSPPS-P as predictor (Model 3), and this model will be compared with the final model that also adds IU (Model 4). In both hierarchical regression analyses, the difference between the models will be tested using an ANOVA.

**Table 1 pone.0256210.t001:** Summary of the regression models.

Models	Predictors	Compared with
Model 1	TA, DELAY-DISCOUNT	
Model 2	TA, DELAY-DISCOUNT, IU	Model 1
Model 3	TA, DELAY-DISCOUNT, SUPPS-P	Model 1
Model 4	TA, DELAY-DISCOUNT, SUPPS-P, IU	Model 3

The comparison between Model 1 and Model 2 will indicate if there is a relationship between IU and p(Wait) after controlling for TA and DELAY-DISCOUNT scores. This is the same comparison that was carried out by Luhmann et al. (2011) [1]. A positive finding in this comparison would replicate their original results. The comparison between Model 1 and Model 3 tests a possible relationship between SUPPS-P and p(Wait) after controlling for TA and DELAY-DISCOUNT scores. Finally, the comparison between Model 3 and Model 4 allows to check if the relationship between IU and p(Wait) is observed after controlling, additionally, for SUPPS-U. These two final comparisons are an extension of the work of Luhmann et al., as described before.

As in Luhmann et al., the association between the same predictors and the median reaction time in trials with an immediate choice will be tested with the same hierarchical regression analyses just described using the median response time in trials with an immediate choice as the dependent variable. This summary will be calculated using the reaction time of all the immediate choice trials of the original condition of the behavioural task (i.e., excluding the check trials).

Two diagnostic plots will be included for each model: a scatterplot of the residuals and predicted values, and a Q-Q plot. If the diagnostic plots show that the linear regression assumptions are not met, a robust linear regression technique (MM-estimates, as implemented by the MASS package in R) will be used.

Two variables will be calculated considering the proportion of delayed choices. The first one will be the proportion of delayed choices when the previous trial was a nonreinforced, delayed-choice trial. The second one, the proportion of delayed choices after any other type of standard trial (i.e., trials after a checking trial will be ignored). As in Luhmann et al., a paired t-test between these two variables will be calculated, as well as the Pearson correlation between the difference of these two proportions.

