Participants will be informed about the conditions of the study and will have to provide their consent to participate. Then, gender and age will be recorded, as well as a set of questionnaires about demographic data and personality traits will be completed online (see Material section for details). Participants will be instructed to read each question in the given order and not to skip questions or go back to an earlier one. After completing them, participants will receive a link that will redirect them to an online platform to perform the decision-making task described in Luhmann et al.’s study. In this task, each trial will begin with the presentation of two empty rectangles displayed on a grey background, side by side on the centre of the computer screen, for a minimum period of time of 0.5 s (see below). Then, the left rectangle will be filled in with two colours (red and green). The colours in the rectangles will provide information about the probability of being and not being rewarded (see Fig 1), which is represented by the size of the green and red areas, respectively (e.g., if both areas have the same size, the likelihood of receiving the reward is 50%). Simultaneously, the monetary value of the reward will be displayed above the rectangle. Selecting this first option (i.e., the immediate choice) will always lead to a 50% chance of receiving a 4 cents reward. Alternatively, participants can wait for the appearance of a delayed choice indicated by the display of the green and red areas in the right rectangle and the offset of these colours in the left rectangle. This delayed choice will always lead to a 70% chance of receiving 6 cents. Immediately after participants select any choice by pressing the spacebar, the rectangle will be completely filled in for 1000 ms with only one colour, green or red, indicating whether or not, respectively, the reward has been gained. Participants will also receive additional information through text messages telling whether they received the reward or not, and the money accumulated so far. The duration of the feedback will be 1 s. To prevent large deviations from the probabilities described to the participants, the task will be pseudorandom. In each block of ten choices of the same type, the number of wins and losses will be fixed (5 and 5 in the case of immediate choices, and 7 and 3 in the case of delayed choices), and their order randomized.

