**Fig 1 pone.0256210.g001:**
[figure not shown]
Sequence of the decision-making task. Left: Trial in which the immediate choice is selected, but no reward is won. Centre: Trial in which the delayed choice is selected, and the reward is won. Right: Check trial to monitor the participant’s engagement, in which an appropriate response is provided, and the reward is won.

Due to the online nature of this study, a new type of trial will be added. Ten check trials will be included to monitor the engagement of participants through the decision-making task. In these trials, the only choice will be a 100% chance of receiving 10 cents, which will be indicated by the display of a new rectangle completely filled in with green colour at the centre of the screen. Participants will be allowed to select this choice by pressing key “E” on their keyboard within three seconds after the rectangle onset. If this choice is not selected within three seconds, or the space bar is pressed, a message will be displayed telling participants that they have missed the possibility of gaining 10 cents. Note that they will have to press a different key (key “E”) on check trials in order to detect automatic or inattentive performance throughout the task. Each check trial will pseudo-randomly appear among the last 5 trials of each 10-trial block. This new type of trials constitutes a modification of the original task but given that participants will be able to complete the task online, it will provide a chance to remove participants that are not adequately paying attention to the task.

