A critical detail of the task is that the delay between the onset of the immediate choice and the delayed choice will vary between 5 and 20 seconds according to a truncated exponential distribution for preventing participants from knowing how long they will have to wait for the second choice. Crucially, participants will be explicitly told that they will not be able to move on to the next trial any sooner by selecting the immediate choice since this action will simply extend the following intertrial interval (ITI). The ITI will follow the same variable time schedule as the delays between choice options. Thus, if in a given trial the programmed delay between choice options is, for instance, 11 s, and the participant takes 2 s to select the first choice, the next ITI will be 9.5 s. It would be the result of adding the 11 s of programmed delay minus the 2 s response time to the minimum ITI duration of 0.5 s. Participants will complete 10 practice trials to familiarize with the task procedure. In these trials, they will be instructed to make specific choices (i.e., on half of the practice trials, they will be directed to select the immediate choice, while on the other half, they will be directed to select the delayed choice) to ensure that they are exposed to the full range of possible outcomes. Two additional practice trials will also be added to get participants familiar with the check trials. In both of them, they will be instructed to press key “E” within three seconds. After practice trials, a total of 100 trials (plus 10 check trials) will be presented. The task will last for approximately 25 minutes.

Participants not completing the entire session and the questionnaires will be excluded from analyses. In addition, participants responding incorrectly on more than two check trials, with more than 10% of reaction times (RTs) below 200 ms when choosing the immediate choice, more than 10% of RTs greater than 3000 ms when choosing the delayed choice, or more than 20 responses to space bar or key "E" during ITI, will be excluded from analyses.

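### The secondary post-loss paired t-test is biased slightly downward even when choices are independent, so its false-positive rate is about 6-12% rather than 5%

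*Protocol article*

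**What the plan says.** The Statistical analysis section defines two variables per participant. "The first one will be the proportion of delayed choices when the previous trial was a nonreinforced, delayed-choice trial". The second is "the proportion of delayed choices after any other type of standard trial (i.e., trials after a checking trial will be ignored". It then states that "a paired t-test between these two variables will be calculated", following the original study, and adds a Pearson correlation that uses the difference. It describes no reference value other than zero, no permutation step and no trial-level model. It also states no direction, hypothesis or alpha for this test; .05 appears only under Planned sample size.

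The design is fixed elsewhere in the article:
- Trials: "a total of 100 trials (plus 10 check trials) will be presented".
- Check trials: "Each check trial will pseudo-randomly appear among the last 5 trials of each 10-trial block".
- Outcome of a wait: "This delayed choice will always lead to a 70% chance of receiving 6 cents". The sequence is controlled: "In each block of ten choices of the same type, the number of wins and losses will be fixed", namely seven wins and three losses for delayed choices.
- Sample: "recruitment will stop as soon as at least 266 participants complete the task" and meet the selection criteria.

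**The concern.** A paired t-test against zero assumes that, with no reaction to losses, the two proportions have the same expectation. Here they do not. The conditioning event, a lost wait, comes from the same choice series as the outcome. If the participant waits again after a lost wait, that wait may also be lost and so add another trial to the denominator. An immediate choice cannot. Sequences with many follow-up waits therefore tend to have larger denominators, and averaging the ratios over people gives those waits too little weight. The first proportion is pulled down and the second slightly up, with no serial dependence in the choices.

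The shift depends on trials per person, so recruiting more people does not reduce it. A larger sample only shrinks the standard error around a wrong centre. At 266 people, 5.4 times the original sample by the article's own count, part of an apparent post-loss effect could be arithmetic.

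**Working it through.** **The plan's own figures.** The article gives no error rate for this t-test, so there is none to reproduce. Its sample size does reproduce. A correlation test with 33% power at n = 49 (3 + 45 + 1) has a target r of 0.219 and needs 266 people for 95% power. The omnibus regression gives f² = 0.081 and 215 people.

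**Inputs.** From the article: 100 standard trials, one check trial per ten-trial block with the next trial dropped, seven wins and three losses per ten delayed choices, 266 people. Assumed: independent choices with personal waiting rate p, two-sided alpha .05, and people with an undefined proportion omitted.

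**Closed form.** Let q = 0.3 be the loss probability, N a person's number of lost waits and S the number of these followed by a wait. To first order the bias of S/N is -Cov(S - pN, N)/E(N)². Only trials that are both follow-up and new conditioning event contribute, each with pq × qp(1-p) = p²q²(1-p). Over n trials:

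- after a lost wait: -n p²q²(1-p)/(npq)² = -(1-p)/n
- after any other standard trial, by the same argument: +qp(1-p)/[n(1-pq)]

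At p = .5 and n = 100 these are -0.0050 and +0.075/85 = +0.0009, a difference of -0.0059.

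**Simulation of the full design**, 4,000 studies per setting. SE is SD/√266.

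| p | Closed-form difference | Simulated difference | SD | SE | Shift in SEs | Rejected (negative tail) |
|---|---|---|---|---|---|---|
| .30 | -0.0077 | -0.0073 | 0.171 | 0.0105 | 0.70 | 11.5% (11.1%) |
| .50 | -0.0059 | -0.0057 | 0.149 | 0.0091 | 0.62 | 9.6% (9.2%) |
| .70 | -0.0038 | -0.0035 | 0.120 | 0.0074 | 0.48 | 7.4% (6.7%) |
| .85 | -0.0020 | -0.0020 | 0.087 | 0.0053 | 0.37 | 6.7% (5.4%) |

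A normal approximation agrees. At p = .5, Φ(-1.96 + 0.62) + Φ(-1.96 - 0.62) = 0.090 + 0.005 = 9.5%. The nominal negative tail is 2.5%.

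**Waiting rates that vary between people.** Rejection was 11.2% for Beta(1,2), 10.2% for Beta(1,1), 10.0% for Beta(2,2), 10.4% for Beta(.5,.5), 8.2% for Beta(4,2), 7.7% for Beta(2,1) and 7.5% for Beta(3,1). The simulation standard error at 10% is √(.1 × .9/4000) = 0.5 points. Smaller repeat runs gave 6.0% at p = .85, 6.1% for Beta(4,1) and 8.2-9.3% for Beta(2,2). If post-check trials were kept, the range would be 6.7-13.1%. Every setting exceeded 5%.

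**Centring.** Each person's difference minus its mean over shuffles of that person's own series gave 4.5-5.8% rejection when choice-outcome records were shuffled together (400 studies per setting). It gave 4.8%, 5.0% and 5.5% for p = .5, Beta(1,1) and Beta(2,1) when choices were shuffled and the outcome schedule kept (1,000 studies each).

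**Lost wait against won wait.** In the closed form q cancels, so the proportion after a won wait has the same first-order bias, -(1-p)/n, and the contrast of the two removes it. In simulation this contrast rejected in about 4-5% of studies under independence, about 5% with 5-point persistence or drift, and 8% with 1-point persistence. The last figure rests on 250 studies (standard error at 5%: √(.05 × .95/250) = 1.4 points) and should be rerun with more.

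**The case against.** The strongest reply is that this is a small bias in a secondary test copied deliberately from the original study, and that real choice series are not independent. Much of that stands. The shift is under one percentage point against a person-level SD of about 9-17 points. Other serial effects can outweigh it: with Beta(2,2) waiting rates, 5-point choice persistence gives a raw mean difference of +0.023 with 69% rejection, and a drift of .4 in p over the session gives +0.032 with 92%. All of these rejections are positive, and none involves a reaction to loss. The cause is that the comparison set includes trials after an immediate choice.

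It does not follow that centring makes matters worse. With 5-point persistence the true value of the planned contrast is about 0.029; the raw mean was 0.023 and the centred mean 0.029. With 1-point persistence the raw test rejects in only 3.3% of studies, but because a real positive difference and the negative bias cancel (mean -0.0001). What does follow is that centring alone cannot turn this contrast into a test of loss reaction: after centring, rejection with no loss effect was still 88% under persistence and 97% under drift.

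A reader might infer that the planned correlation is also distorted. The article does not name its second variable. Taking it to be IU, with a correlation of -.22 with p(Wait) and independent choices, the induced correlation was -.002 to -.007 and rejection 4.7-5.2%, which is about nominal. A nearly constant shift does little to a correlation.

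**Conclusion.** The point holds for the paired t-test as the article describes it. The expected difference under independent choices is about -0.2 to -0.8 percentage points, and the two-sided false-positive rate about 6-12%, mostly in the direction of less waiting after a lost wait. The rate depends on the p(Wait) distribution, which the article does not give: about 6-8% if most people mostly wait, about 9-12% at mean waiting rates of .3-.5. Alpha of .05, two-sided, is also an assumption for this test.

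Three stronger readings are not supported. The replication criterion, the comparison of Models 1 and 2 on p(Wait), does not use these proportions and is unaffected. Nothing in the article says the test is looking for less waiting after losses, so the bias cannot be said to favour a stated hypothesis. No material harm to the correlation was shown. The posted R script is not part of the document, so this conclusion concerns the described analysis only.

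**What to change.** Decide the following before the data are seen, and add it to the Statistical analysis section and the posted script:

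1. For each participant, shuffle the order of the 100 choice-outcome records (for example 1,000 times), recompute the planned difference each time and subtract the mean of these values from the observed difference. Run the paired comparison on the centred differences.
2. Report the uncentred test as well, labelled as the comparison with the original study.
3. Add a contrast of waits after a lost wait with waits after a won wait, and rest any conclusion about reacting to loss on it. Both sets follow a delayed choice, so persistence or drift alone should not produce a difference.

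The cost is a few lines of script, a few sentences of text and a departure from the original study's exact test, which is still reported. No new data are needed.

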### Exploratory analysis

Exploratory analyses [43,44] will be carried out to separately study the role of the different factors of the SUPPS-P scale [45], as well as the prospective and the inhibitory factors of IU scale [46]. We have no specific hypothesis regarding each subscale and factor, and all statistical analysis will be performed accordingly.

### Data collection and storage

Data collection is expected to begin in mid-November, 2021. The behavioural data and questionnaire scores will be available at the OSF repository at https://osf.io/qyk87/?view_only=556eed2f698b472ca6767e763f768e16, with unrestricted access, as soon as the data collection has been completed. The data will be completely anonymized, and the original data with identifiers will be deleted. The R script with all of the analyses described are already available at https://osf.io/b8hfc/.

## Implications of the expected results

The consideration of IU as a main source of maladaptive and inefficient behaviour and decision making that may severely affect people suffering from anxiety-related mental disorders has been widely postulated in the literature, but this claim lacks empirical support [2]. As far as we know, Luhmann et al.’s study [1] provides the clearest evidence showing that people scoring high in IU tend to choose options that are riskier and less valuable as long as they imply less time waiting in an uncertain situation. This strongly suggests that many examples of costly behaviour in anxiety-related psychopathologies, such as excessive avoidance, may be understood as instances of decisions aimed to avoid time enduring uncertainty [see also 13,14]. Moreover, Luhmann et al.’s results also suggest that the same mechanism may underlie many instances of high-cost decision making in the non-clinical population. The results of our proposed study will be informative whether a significant association between IU and willingness to wait is found or not. In the former case, Luhmann et al.’s results will have been replicated, at least in essence, with a much larger sample, and with additional analyses that will refine our understanding of the relationship between IU and willingness to wait. In the latter case, our results may indicate that there is an underdetermination of the original hypothesis that would need to be taken into account in order to better describe the relation between IU and the behavioural task used by Lumann et al.

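### The benchmark effect that sets n = 266 is never compared with the IU estimate, so the stated reading of a non-significant result understates what the design can conclude

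*Protocol article*

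**What the plan says.** Under Planned sample size, the article adopts the small-telescopes approach, in which "the target effect size would be the effect size that can be detected with a power of 33% in the original study". For the IU coefficient it reports that this effect "is f^2^ = 0.049, and the sample size required to detect this effect with a power of 95% would be n = 266".

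Under Statistical analysis, IU is assessed by comparing nested models (Model 1 with Model 2, and Model 3 with Model 4): "In both hierarchical regression analyses, the difference between the models will be tested using an ANOVA". On Model 1 against Model 2 the article states: "A positive finding in this comparison would replicate their original results". The rest of that section covers reaction-time models, diagnostic plots with an MM-estimate fallback, a paired t-test and a correlation. Exploratory analysis adds subscales. No described analysis sets the IU estimate, or an interval for it, beside f² = 0.049.

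Implications of the expected results says the study will be informative whether or not the association is significant. For the non-significant case the only reading given is that "our results may indicate that there is an underdetermination of the original hypothesis that would need to be taken into account".

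**The concern.** The benchmark is derived with care, fixes the recruitment target, and then drops out of the plan. The nested-model ANOVA has zero as its null value. A non-significant result is therefore not, as written, a statement about whether the effect is smaller than one the original study had a reasonable chance of detecting. That is the question the benchmark is suited to answer.

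At stake is what may be concluded if the finding does not replicate. The article promises an informative null but describes it in terms that carry no effect size. A reader of the eventual report could take a null for an ambiguous outcome when the data in fact rule out the benchmark.

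**Working it through.** **Inputs, all from Planned sample size.** In the original study "that multiple regression model had 3 degrees of freedom in the numerator and 45 in the denominator", so N = 45 + 3 + 1 = 49. Alpha is 0.05, power 95%, and the IU target f² = 0.049 with n = 266.

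**The plan's own figures reproduce.** Noncentral F, noncentrality λ = N·f²:
- Omnibus test, 3 and 45 df, 33% power: f² = 0.0814, and 95% power needs 214.9 (stated: 0.081 and 215).
- IU coefficient, 1 and 45 df, 33% power: f² = 0.0492, and 95% power needs 266.1 (stated: 0.049 and 266).
- Power at n = 266 for f² = 0.049: 94.9%.

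**Benchmark as a partial correlation.** |r| = √(f²/(1 + f²)) = √(0.049/1.049) = 0.216. The original association was negative, so the benchmark is -0.216. Fisher z = 0.2195.

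**Cut-off for excluding the benchmark.** Model 2 has two covariates besides IU, so SE = 1/√(266 − 3 − 2) = 1/√261 = 0.0619. A 90% CI excludes the benchmark when |z| < 0.2195 − 1.645 × 0.0619 = 0.1177, that is, when the estimate is weaker than r = -0.117.

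**Cut-off for significance against zero.** Two-sided 5%, 262 df, t = 1.969: |r| = 1.969/√(262 + 1.969²) = 0.121.

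**The gap between them.** In units of SE it is about (0.1216 − 0.1177)/0.0619 = 0.063. The probability of landing there is at most about 0.063 × 0.399 = 0.025, whatever the true effect. The noncentral t calculation (262 df, noncentrality √(0.049 × 266) = 3.61) puts the cut-offs closer still: t = 1.961 for excluding the benchmark against 1.969 for significance. If f² is varied within its rounding (0.0485 to 0.0495), the first runs from 1.943 to 1.980, so the two are equal for practical purposes.

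**Power to show that the effect is weaker than -0.216** (one-sided 5%, Fisher z):

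| True partial r | Calculation | Power |
|---|---|---|
| 0 | Φ(0.1177/0.0619) = Φ(1.90) | 97% |
| -0.05 | Φ((0.1177 − 0.0500)/0.0619) = Φ(1.09) | 86% |
| -0.10 | Φ((0.1177 − 0.1003)/0.0619) = Φ(0.28) | 61% |
| -0.108 (half the benchmark) | Φ((0.1177 − 0.1084)/0.0619) = Φ(0.15) | 56% |

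The noncentral t version gives 97.5% at zero, 85% at a quarter of the benchmark and 56% at half.

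**The case against.** The strongest reply is that the primary test already settles the matter. With about 95% power at f² = 0.049, non-significance has only about a 5% chance if the true effect equals the benchmark. The near-identical cut-offs show that the added comparison would seldom alter a decision. That stands: the change is to what a null may be said to show, not to whether the finding counts as replicated. The article never draws this inference, however, and its closing sentence points to a weaker one.

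Second, the article invokes the small-telescopes approach only to choose a target effect and does not promise a test against it. That also stands, so there is no broken commitment. The case rests on the article's own f², n and reading of a null, not on what the cited method may require.

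Third, the quoted sentence is hedged discussion in a condensed article, and the public script is not shown. But the article says the script holds the analyses described, and none of those uses the benchmark. The sentence is also the only place where the article says what a null would mean.

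A reader might infer something stronger: that half of the study's question has no inferential rule. The documents do not support this. Alpha, target effect, power, models and the replication criterion are all stated. What is missing is the explicit link from a null to the benchmark.

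**Conclusion.** The point holds as an improvement to interpretation and reporting. The IU estimate is never set against the effect that justified n = 266, and the stated reading of a non-significant result says less than the design can deliver. At n = 266 almost every non-significant result would also exclude a partial correlation of -0.216.

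Two further inferences are not supported. The sample size and primary test are not in error: the planning figures reproduce and the nested-model comparison is a valid test of IU. Nor does this sample always give a firm answer: power to exclude the benchmark is about 56–61% if the true effect is about half of it, and excluding it never proves a zero effect.

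The figures assume exactly 266 analysed participants, ordinary least squares in Model 2 with two covariates, f² = 0.049 as rounded, and a one-sided 5% comparison in the original direction. Recruitment stops at 266 or more, so the achieved n may be larger. The two cut-offs then separate. They meet when √(n − 5) = (1.960 + 1.645)/0.2195 = 16.42, that is, at n of about 275. Above that, a weak but significant result can also exclude the benchmark, so the readings should cover that case.

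**What to change.** In Statistical analysis, add that the signed IU partial correlation from Model 2 will be reported with its 90% CI and read against -0.216 (f² = 0.049) as follows:

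- **Significant and negative:** replicated, noting whether the CI excludes -0.216.
- **Not significant, CI excludes -0.216:** the effect is smaller than the one the original study had 33% power to detect. This does not show that it is zero.
- **Not significant, CI includes -0.216:** inconclusive.
- **Significant and positive:** not a replication.

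If the MM-estimate fallback is used, report the corresponding 90% interval for the IU coefficient and say beforehand how f² = 0.049 is put on that scale. One option is -√0.049 = -0.221 times the residual scale, divided by the standard deviation of IU after adjustment for the other predictors.

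Reword the last sentence of Implications of the expected results to match these readings.

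The cost is one interval from a model already planned and a few sentences, with no more participants. It should be fixed before the data are seen.
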